### Participant timeline {13}

The study design and participant timeline are detailed in Fig. 1 and encompass a minimum of 1 and a maximum of 3 different study vaccines. Table 1 details the schedule of activities. Participants will have up to 7 visits during the study period, with follow-up continuing for 12 months following their final study vaccine. Participants randomised to receive one study vaccine will have 5 study visits, while those randomised to two doses of vaccine will have 7 visits. Participants following assigned study procedures can remain on the study for 13 to 16 months.

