### Sample size {14}

The maximum sample size is 960 participants, including 320 in each of the HIV, SOT, and haematological malignancy groups. This maximum sample size is based on simulations conducted prior to trial commencement for estimating the primary outcome (anti-spike SARS-CoV-2 IgG antibodies 28 days after completion of trial vaccine/s) for different trial strata (clinical group [HIV, SOT, haematological malignancy], vaccine brand, SARS-CoV-2 serostatus at enrolment) with sufficient precision. The simulations are detailed in the Statistical Appendix and will be published separately.

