## Assignment of interventions: allocation

### Sequence generation {16a}

Participants will be assigned to an arm using a central computer-generated random allocation algorithm. Randomisation will be stratified by study subgroup (HIV, SOT, haematological malignancy).

Participants will be equally randomised to one of the available vaccine arms if an intervention arm is dropped after an interim analysis or following a recommendation from the data safety management committee, then future participants will be equally allocated to the remaining arms.

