## Statistical methods

### Statistical methods for primary and secondary outcomes {20a}

Baseline demographic and anthropometric data as well as the defined safety and immunogenicity outcome measures will be stratified by study cohort (HIV, SOT, haematological malignancy) and summarised with appropriate measures of spread. Immune responses and reactogenicity to COVID-19 vaccines will be assessed on a modified intention-to-treat population, depending on actual intervention received between randomisation and providing blood samples for the primary endpoint. Participants with SARS-CoV-2 infection or antibody therapy (e.g. IVIG), between randomisation and providing blood samples will be excluded from the primary analysis. For safety reporting, participants will be included in the intervention group that they received, irrespective of the intervention they were randomised to.

The primary outcome will be the anti-spike IgG antibody against SARS-CoV-2, 21–35 days after completion of study vaccines, summarised as the GMC. Participants who miss a study blood draw, have SARS-COV-2 infection diagnosed by RAT, PCR or anti-nucleocapsid antibodies, or obtain an unscheduled dose of COVID-19 vaccine between the time of randomisation and the primary endpoint will be excluded from analysis. A Bayesian hierarchical two-part model will be used for the primary analysis as it is anticipated that a significant proportion of primary outcomes may be below the assay limit of detection.

Secondary endpoints described above will be analysed depending on the type of outcome; continuous immunological variables will be modelled with the two-part Bayesian model described; binary endpoints, including safety endpoints, will be analysed using a Bayesian logistic model; a Bayesian Poisson regression will be used to compare counts and rates. Further statistical detail is available in the statistical appendix which will be published separately.

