## Discussion

BOOST-IC is a multi-centre, adaptive randomised clinical trial to assess the immunogenicity and safety of alternative booster regimens of COVID-19 vaccines in immunocompromised groups. This includes those living with HIV, solid organ transplantation, and certain haematological malignancies.

This study builds on local and international evidence that the study’s target populations are more likely to experience poorer outcomes following infection with SARS-CoV-2 and to have suboptimal immunological responses to current immunisation schedules. While the availability of COVID-19-targeted antivirals reduces the risk of severe infection, they are not licensed or proven to be effective for prevention. Administration of monoclonal antibodies, either alone or in combination, has previously proved useful in people unable to mount effective humoral responses. However, these are expensive, challenging to access, and their efficacy has been limited by the rapid evolution of SARS-CoV-2 variants characterised by their capacity to escape existing neutralisation responses. Hence, the development of endogenous immunological responses through vaccination remains an essential component of prevention strategies for COVID-19 in these groups.

Strengths of this study include its pragmatic design and its assessment of both immunological and safety outcomes. Immunological responses will be assessed objectively, while the blinding of participants and assessors to vaccine type and schedule will reduce contamination of responses. Additional strengths include the inclusion of a broad range of participants and levels of immunocompromise, and the design allows the inclusion of additional new vaccines as they become available.

Limitations of this study include the heterogeneous nature of enrolled participants with different immunosuppressive regimens, levels of hybrid immunity due to past infection and numbers and types of COVID-19 vaccines. Similarly, this study is conducted in the context of community transmission of COVID-19, and evolving COVID-19 policy which may influence trial participation, the desire by participants and their usual clinicians to obtain additional vaccines and therapies outside of the trial, which may affect results, introduce protocol deviations, or trial completion.

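### Poisson regression is the only model named for counts and rates; without a term for between-participant variation, intervals for recurrent outcomes such as healthcare utilisation would be too narrow if counts are overdispersed

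*Protocol article*

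**What the plan says.** The protocol article, Statistical methods {20a}, allocates models by a general rule: "Secondary endpoints described above will be analysed depending on the type of outcome". Continuous immunological variables go to the two-part Bayesian model, binary endpoints to a Bayesian logistic model, and for the rest "a Bayesian Poisson regression will be used to compare counts and rates". The section then adds: "Further statistical detail is available in the statistical appendix which will be published separately".

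Outcomes {12} ends its clinical list with healthcare utilisation: outpatient medicines and services, and inpatient admissions, linked to COVID-19 or the study vaccines. Most other clinical outcomes in that list (infection, death, oxygen or ventilatory support, intensive care) read as yes/no per participant. Healthcare utilisation is not named in {20a}, so its link to the Poisson clause is an inference from its type, though a direct one.

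The Discussion acknowledges the mix of participants: "Limitations of this study include the heterogeneous nature of enrolled participants with different immunosuppressive regimens". It adds differing hybrid immunity and vaccine history.

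**The concern.** A Poisson likelihood sets the variance of a participant's count equal to its mean, given the covariates in the model. Service use rarely behaves like that. A single infection or vaccine reaction can bring a run of visits, prescriptions and perhaps an admission in the same person, while many participants contribute zero. Disease group and other covariates would explain part of this spread, but hardly the run of contacts that follows one episode. The variance across participants then exceeds the mean.

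A Poisson model with no term for the excess treats the total event count as the amount of information, when the information really comes from the number of participants. The posterior for the rate ratio between booster strategies is then too concentrated, and a few heavy users falling by chance in one arm can look like a difference between strategies.

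**Working it through.** **Inputs from the article.** Maximum size: "The maximum sample size is 960 participants, including 320 in each of the HIV, SOT, and haematological malignancy groups". Allocation: "Participants will be equally randomised to one of the available vaccine arms". Two vaccines are under study, each with one or two doses. Treating these as four equal arms (an assumption) gives 960/4 = 240 per arm; a pooled two-way comparison gives 960/2 = 480 per side.

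**Inputs that the article does not give.** There is no mean count, dispersion, prior or covariate list for count outcomes, and the sample size was set on the primary IgG outcome. There is thus no figure of the plan's own to reproduce. Everything below is an illustration over an assumed range.

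**Formula.** Let each participant's count have mean *m* and variance φ*m*, with *n* participants and S = *nm* events in an arm.

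- True variance of the log rate: φ*m*/(*n m*²) = φ/S.
- Variance assumed by Poisson: 1/S.
- The Poisson standard error is therefore too small by a factor √φ, whatever *n* is.
- With no true difference, a nominal 95% interval excludes a rate ratio of 1 with probability 2 × [1 − Φ(1.96/√φ)].

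If participants' rates follow a gamma distribution with shape *k*, then φ = 1 + *m*/*k*.

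**Results.**

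| φ | Example (*m*, *k*) | √φ | 1.96/√φ | False-difference rate |
|---|---|---|---|---|
| 1.00 | no overdispersion | 1.00 | 1.960 | 5.0% |
| 1.15 | 0.3, 2 | 1.07 | 1.828 | 6.8% |
| 1.60 | 0.3, 0.5 | 1.26 | 1.550 | 12.1% |
| 2.00 | 2, 2 | 1.41 | 1.386 | 16.6% |
| 3.00 | 1, 0.5 | 1.73 | 1.132 | 25.8% |
| 5.00 | 2, 0.5 | 2.24 | 0.877 | 38.1% |

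**One case in full.** With 240 per arm, *m* = 1 and *k* = 1, S = 240 in each arm and φ = 2.

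- Poisson standard error: √(2/240) = 0.091. Around an estimated rate ratio of 1 the interval is exp(±1.96 × 0.0913), or 0.84 to 1.20.
- Correct standard error: √(2 × 2/240) = 0.129. The interval is exp(±1.96 × 0.1291), or 0.78 to 1.29.

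**Simulation check.** Gamma-Poisson counts with no arm difference, 4,000 runs per setting, 240 per arm, gave 5.1% at φ = 1, 13.3% at 1.6, 16.3% at 2, 25.7% at 3 and 37.3% at 5. Results at 480 per arm were close to these (12.5%, 16.6%, 25.5% and 37.8% for φ = 1.6 to 5), so a larger trial does not cure the problem. When the standard error came from the observed between-participant variance, the rate was 4.3% to 5.8% in every setting. A separate simulation at 160 per arm gave 6% for the φ = 1.15 case, slightly under the formula's 6.8%.

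These are large-sample Wald intervals. They stand in for Bayesian intervals under weak priors, which is a further assumption, because the article states no priors. The simulations contain no covariates, so all heterogeneity is left unexplained by construction.

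**Person-time.** The article says that "Participants following assigned study procedures can remain on the study for 13 to 16 months", and the longer stay belongs to the two-dose arms. If events are counted from randomisation, exposure differs by dose arm by up to 16/13 = 1.23. This is why the model needs an offset as well as a dispersion term.

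**The case against.** The strongest reply is that the article names a model family and nothing more. A reader might infer that it commits the trial to a plain Poisson model that treats every event as independent, and hence that the intervals are too narrow and false differences will appear. The text does not support that reading. It neither includes nor excludes a random effect, dispersion term or offset, and it defers further detail to an appendix that is not shown. A Poisson model with a participant-level random effect is still a Bayesian Poisson regression, so one form of the remedy already fits the published sentence.

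Three further objections carry weight. Healthcare utilisation is tied to this model only by inference, and if it were scored as any use versus none, the logistic model would apply. Equal rates are needed only given the covariates, which are not listed. The larger error rates need ratios of 2 or more, while an outcome restricted to use related to COVID-19 and the study vaccines may have a low mean, where the effect is modest.

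All of this limits the claim without removing it. The sentence makes a positive choice of likelihood for counts. In the same section the primary model is described as hierarchical and two-part, with a reason drawn from the expected data; the count clause has no such qualifier. Naming a model that absorbs overdispersion is better than leaving it open, and costs almost nothing.

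**Conclusion.** The point holds conditionally and is minor. If the named Poisson regression is applied without a dispersion or participant-level term to recurrent counts, and those counts are overdispersed, intervals for arm comparisons will be too narrow by √φ. Overdispersion is likely here, given clustered contacts within an episode and a mixed population, but its degree cannot be read from the article. Over the assumed range, the false-difference rate is about 7% to 12% for φ of 1.15 to 1.6, and about 17% to 38% for φ of 2 to 5, against a nominal 5%.

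Only secondary count outcomes are touched. The primary IgG outcome has its own model, the interim analyses and precision thresholds concern that outcome, and no decision rule in the article uses healthcare utilisation.

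**What to change.** In Statistical methods {20a}, replace the clause on counts and rates with wording such as: *Counts and rates will be compared with a Bayesian negative binomial regression (or a Poisson regression with a participant-level random effect), with log person-time as offset.* Align the statistical appendix if it does not already do this; if it does, only the article's sentence needs to match. A Poisson model without the extra term can be kept as a sensitivity analysis.

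The cost is one sentence and a different likelihood or one extra term in the model. Intervals for these secondary outcomes will be somewhat wider if the counts are overdispersed. If they are not, both models come close to the Poisson and little is lost.

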### Interim analyses {21b}

The first analysis of the primary outcome will be performed after 260 eligible participants have completed 21–35 days of follow-up after receipt of their final study vaccine, and the results from the batched blood samples are available from the laboratory analysis. Subsequent analyses will be performed after every 100 additional participants have available laboratory results for the remainder of the trial until the maximum recruitment of 960 participants is reached.

### Methods for additional analyses (e.g. subgroup analyses) {20b}

Additional analyses may be conducted to examine for statistical interactions between anti-spike IgG serostatus at baseline, reported COVID-19 infection, number and type of vaccine doses received prior to randomisation, and type and intensity of immunosuppression received.

### Methods in analysis to handle protocol non-adherence and any statistical methods to handle missing data {20c}

No modifications or corrections to the endpoint will be made due to non-adherence to allocated intervention, in the context of a serious adverse event, or where non-adherence is due to site procedures or availability. In contrast, participants with missing data (e.g. blood draw) due to lost to follow-up or withdrawal from the study will be excluded from the analyses.

### Plans to give access to the full protocol, participant-level data and statistical code {31c}

The trial protocol and statistical code used for analyses will be made publicly available following publication of the primary results in the academic literature. Deidentified participant-level data may be made available upon reasonable request to the principal investigator after the publication of the results.

## Oversight and monitoring

### Composition of the coordinating centre and trial steering committee {5d}

The coordinating trial centre is located at the Department of Infectious Diseases at Alfred Hospital, in Melbourne. The Trial Steering Committee (TSC) is chaired by the Principal Investigator (PI) and includes representatives from the clinical, laboratory, statistical disciplines and consumer representatives. The TSC is responsible for the study conception, drafting, and completion of the study protocol and associated documents, recruitment plan, data monitoring and integrity, endpoint adjudication, and approving publications arising from the study.

### Composition of the data monitoring committee, its role and reporting structure {21a}

The Data Safety Monitoring Committee (DSMC) will consist of at least 3 members, and up to 6 members. The Chair will have expertise in clinical trial methods. Additional medical, and statistical experts will be selected to ensure the necessary expertise to oversee the trial, including an understanding of Bayesian adaptive clinical trials. The DSMC will meet at least three times per year to monitor and review accumulating safety reports and will make recommendations to the CPI on whether there are any ethical or safety reasons why the trial should not continue or should be modified prior to continuation. The DSMC will also review accumulating trial data for the primary analysis at pre-specified times detailed in the statistical appendix. The results of these analyses will be provided confidentially to the DSMC as an unblinded report, including recommendations to continue or stop recruitment into each stratum depending on whether the precision threshold has been met.

The Chair of the DSMC will be contacted for advice and independent review in the following situations: Following any SUSAR, a decision threshold is met, and any other situation where the Investigator feels independent advice or review is important. Full details of the DSMC’s function and workings are detailed in the trial DSMC charter.

### Adverse event reporting and harms {22}

This study will collect data on both solicited and unexpected adverse events (AE) following study intervention. At each contact with the participant, information will be sought on adverse events and details recorded in the eCRF. Solicited AEs are those events specifically captured in the diary card up to 7 days after each vaccination and for this study include pain, induration, erythema, temperature, headache, fatigue, chills, myalgia, joint pain, nausea, diarrhoea, chest pain.

Serious adverse event (SAE) is one which is deemed medically significant; warrants hospitalisation or emergency department presentation; results in congenital anomaly or permanent disability or incapacitation; and is life-threatening or causes death. SAEs are monitored continuously and have special reporting in the eCRF, and to the study sponsor and HREC within 24 h of an investigator becoming aware. All SAEs that occur from randomisation up to 28 days following the last dose of an investigational product will be documented and reported; SAEs that occur thereafter will only be documented and reported if they are deemed to be at least possibly related to the study vaccine. Suspected unexpected serious adverse reactions (SUSARs) are any SAE that is both suspected to be related to the trial treatment and is unexpected (i.e. not consistent with the available safety information in the investigator’s brochure (for unapproved products)/approved product information. A specific list of adverse events, and adverse events of special interest are defined and will be recorded if occurring throughout the course of the study for participants [39].

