**Methods:**

Bringing optimised COVID-19 vaccine schedules to immunocompromised populations (BOOST-IC) is an adaptive randomised trial of one or two additional doses of COVID-19 vaccines 3 months apart in people living with HIV, solid organ transplant (SOT) recipients, or those who have haematological malignancies (chronic lymphocytic leukaemia, non-Hodgkin lymphoma or multiple myeloma). Key eligibility criteria include having received 3 to 7 doses of Australian Therapeutic Goods Administration (TGA)-approved COVID-19 vaccines at least 3 months earlier, and having not received SARS-CoV-2-specific monoclonal antibodies in the 3 months prior to receiving the study vaccine. The primary outcome is the geometric mean concentration of anti-spike SARS-CoV-2 immunoglobulin G (IgG) 28 days after the final dose of the study vaccine. Key secondary outcomes include anti-spike SARS-CoV-2 IgG titres and the proportion of people seroconverting 6 and 12 months after study vaccines, local and systemic reactions in the 7 days after vaccination, adverse events of special interest, COVID-19 infection, mortality and quality of life.

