### Outcomes {12}

The primary outcome is defined as the geometric mean concentration (GMC) of anti-spike IgG antibody against SARS-CoV-2, 28 days after completion of trial vaccine/s, i.e. after one or two doses in the respective trial arms.

Secondary outcomes include laboratory, safety and clinical outcomes:

Laboratory outcomesThe GMC of anti-spike IgG antibody against SARS-CoV-2, 6 and 12 months after completion of trial vaccine/sThe proportion of participants seropositive to SARS-CoV-2 IgG, 1, 6 and 12 months after completion of trial vaccine/sThe GMC of anti-spike IgG antibody targeting specific SARS-CoV-2 variants, 1, 6 and 12 months after completion of trial vaccine/sThe SARS-CoV-2 neutralising antibody response, 1, 6 and 12 months post completion of trial vaccine/s, in a subset of participants with response defined as either rise in the neutralising antibody titreο Fourfold rise in the neutralising antibody titre for those with detectable neutralising antibodies at baseline, ORο Detectable neutralisation in those with no detectable neutralising antibodies at baselineThe magnitude of SARS-CoV-2 specific T-cell responses, 1, 6 and 12 months post completion of trial vaccine/s in a subset of participantsSubset analysis and polyfunctionality (number of effector cytokines) of SARS-CoV-2 specific T-cell responses, 1, 6 and 12 months post completion of trial vaccine/s in a subset of participants

Safety outcomesLocal and systemic reactions assessed on days 1, 2, 3, 4, 5, 6 and 7 after randomisation.Hospitalisation resulting from adverse events following immunisation (AEFI) up to day 28.Adverse events of special interest (AESI) up to 12 months post completion of trial vaccine/s

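### All-cause SAE recording ends near D28 with one dose but D112 with two, and 12-month event windows end at D365 versus D455 with no stated start, so the randomised schedules are not compared over equal exposure

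*Protocol article*

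**What the plan says.** The abstract describes an "adaptive randomised trial of one or two additional doses of COVID-19 vaccines 3 months apart", so the number of doses is a randomised factor. Table 1 (Schedule of activities) puts the second dose at D84, the visit 28 days after it at D112, and the last visit at D365 for one dose and D455 for two.

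Two sets of event windows are tied to the last dose:

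- **SAEs** (Adverse event reporting and harms {22}): "All SAEs that occur from randomisation up to 28 days following the last dose of an investigational product will be documented and reported". After that, "SAEs that occur thereafter will only be documented and reported if they are deemed to be at least possibly related to the study vaccine".
- **AESI and clinical outcomes** (Outcomes {12}): "Adverse events of special interest (AESI) up to 12 months post completion of trial vaccine/s". SARS-CoV-2 infection, medically attended infection, death, oxygen or ventilatory support and ICU care end at the same point. None of these entries says when counting starts. Participant timeline {13} agrees on the end, "with follow-up continuing for 12 months following their final study vaccine".

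On analysis, section {20a} says "binary endpoints, including safety endpoints, will be analysed using a Bayesian logistic model", and "a Bayesian Poisson regression will be used to compare counts and rates". It gives no common window or exposure term for the events above and refers further detail to a statistical appendix that is not shown.

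**The concern.** A window that ends relative to the last dose is longer, measured from randomisation, for people given a second dose 84 days later. If events accrue at the same rate in both schedules, the longer window collects more of them. The difference then looks like an effect of the second dose when it is only time at risk.

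The SAE rule matters most because it governs what is collected. From D29 to D112 one schedule has SAEs of any cause and the other has only those judged possibly related. The only all-cause window common to both schedules under the present rule is D0 to D28, when everyone has had one dose, so it says nothing about the second.

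At stake is the one- versus two-dose safety comparison in a trial whose objectives include confirming the safety of one or two doses. For infection, the longer two-dose window would also work against showing any protection from the second dose.

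**Working it through.** **1. Windows from the schedule.** Day of last dose plus window length:

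| Window | One dose | Two doses | Ratio |
|---|---|---|---|
| 28 days after last dose | 0 + 28 = D28 | 84 + 28 = D112 | 112/28 = 4.0 |
| 12 months after last dose | 0 + 365 = D365 | 84 + 365 = D449; scheduled D455 | 455/365 = 1.25 (449/365 = 1.23) |

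These reproduce Table 1. D449 and D455 differ by 6 days, inside the 30-day visit tolerance.

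**2. Expected difference under no effect.** The article gives no event rates, so the one-dose risk p1 is assumed over a range. With the same constant hazard in both schedules, p2 = 1 − (1 − p1)^(T2/T1) and OR = [p2/(1 − p2)] / [p1/(1 − p1)].

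SAEs, T2/T1 = 4 (example: 1 − 0.98^4 = 0.0776):

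| Assumed 28-day risk | Two-dose risk | OR |
|---|---|---|
| 0.5% | 2.0% | 4.03 |
| 1% | 3.9% | 4.06 |
| 2% | 7.8% | 4.12 |
| 5% | 18.5% | 4.33 |

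12-month events counted from randomisation, T2/T1 = 455/365:

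| Assumed 12-month risk | Two-dose risk | OR |
|---|---|---|
| 2% | 2.5% | 1.25 |
| 5% | 6.2% | 1.25 |
| 10% | 12.3% | 1.26 |
| 20% | 24.3% | 1.28 |
| 30% | 35.9% | 1.31 |
| 40% | 47.1% | 1.34 |

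Using 449 days instead lowers these odds ratios to between 1.23 and 1.31.

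**3. How often the artefact would look like a signal.** Section {14} states: "The maximum sample size is 960 participants, including 320 in each of the HIV, SOT, and haematological malignancy groups". I assume a 1:1 split by dose number, so n = 480 per schedule overall and 160 within a clinical group. The yardstick is a one-sided 0.025 level. The article sets no such rule, so this only illustrates scale. With p̄ the mean of p1 and p2, the probability is Φ(z), where z = [(p2 − p1)√n − 1.96√(2p̄(1 − p̄))] / √[p1(1 − p1) + p2(1 − p2)].

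- SAEs at 0.5%, 1%, 2% and 5%: 0.55, 0.84, 0.99 and 1.00 with 480 per schedule; 0.22, 0.40, 0.67 and 0.97 with 160.
- 12-month events at 2%, 5%, 10%, 20%, 30% and 40%: 0.07, 0.12, 0.21, 0.36, 0.49 and 0.60 with 480 per schedule; 0.05 to 0.25 with 160.

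A simulation with Beta(0.5, 0.5) priors, flagging a posterior probability above 0.975, agrees at 480 per schedule: 0.86 for SAEs at 1% and 0.36 for infection at 20%. With equal windows, the simulated rate falls to about 0.02 to 0.03.

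**4. The other reading of the start.** If clinical events count from completion, both windows last 12 months. Events from D0 to D84 are then dropped for two-dose participants only, who must also have reached dose 2 to be counted. Neither reading gives a like-for-like randomised comparison.

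**The case against.** Four objections have weight.

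- **All-cause SAEs are not on the outcome list in {12}.** The listed safety outcomes are reactions on days 1 to 7, AEFI hospitalisation to day 28, and AESI. Section {22} sets a documentation and reporting window. A reader might infer that the planned logistic model will return an SAE odds ratio of about 4; the text does not establish that. The figure applies to any table of SAEs by schedule.
- **The unseen appendix may define common windows or offsets.** This stands for AESI and clinical outcomes, where the article already plans a rate model. It does not stand for SAEs that were never documented.
- **The data loss is narrower than it looks.** After D28, one-dose participants still contribute possibly related SAEs, deaths, COVID-19 events and AESI. What is missing is other SAEs judged unrelated, D29 to D112.
- **Truncation at D365 needs event dates.** The article does not say these are recorded. The M12 visit is for one-dose participants only; two-dose participants are seen at M9 and M15.

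A reader might also infer that the DSMC will see a false safety signal. Section {21a} describes review of safety reports by a committee with statistical expertise and gives no between-arm SAE rule, so this is conjecture.

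**Conclusion.** The point holds in a limited form. The unequal SAE recording is written into the harms section, gives a 4:1 exposure ratio, and cannot be repaired at analysis. For AESI and clinical outcomes the defect is an end point tied to the last dose with no stated start. The resulting distortion is modest, with an odds ratio of about 1.25 to 1.34 under no effect if counting starts at randomisation.

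The sizes rest on a constant hazard and assumed event rates; the exposure ratios do not. It might be inferred that mortality and ICU results are seriously compromised. The arithmetic does not support that: at risks of 2% to 5% the artefact alone would cross the yardstick in only 0.07 to 0.12 of trials with 480 per schedule. The primary outcome and brand comparisons at equal dose number are unaffected. Outcomes not tied to the last dose (solicited reactions, AEFI hospitalisation to day 28) fall outside this point.

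This should be fixed. It does not undermine the trial's main result, but the SAE change should be prompt because unrecorded events are lost.

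**What to change.** 1. **SAE recording.** Document all-cause SAEs from randomisation to D112 in every arm, or to 28 days after the last dose if later, since the 7-day tolerance on the D84 visit can move that point to between D105 and D119. For one-dose participants use the M6 visit: section {18a} already has nurses ask at every visit about SAEs since the previous one. Compare schedules over D0 to D112, and give 28-day windows after each dose as description.
2. **AESI and clinical outcomes.** State that comparisons run from randomisation to D365 in all arms. Require event dates, in particular at the two-dose M15 visit, so that events can be placed before or after D365. Report later events descriptively.
3. **Where follow-up still differs**, use the planned Poisson model with a person-time offset in place of a logistic model of any event.

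With a common window or person-time rates, the expected ratio under no effect in the setting above is 1.00. The cost is revised wording in {12}, {20a} and {22}, slightly more SAE recording in one-dose arms at an existing visit, and the loss of two-dose events after D365 from the main comparison.
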